
### Secondary determinants and potential confounders

As potentially interesting determinants and confounding variables, we will assess age, sex, level of education, partner status, the BIG-five personality traits, early and recent life-events, extent of social network, loneliness, lifestyle characteristics (including alcohol usage, smoking, sleep, physical activity) and self-management abilities.

The Big Five personality traits –openness to experience, conscientiousness, extraversion, agreeableness and neuroticism- will be assessed using the NEO Five Factor Inventory (NEO-FFI) [56]. Negative life events in childhood and adolescence concerning emotional, physical and sexual abuse were will measured with the NEMESIS questionnaire [57]. The list of threatening experiences [58] will be used to inquire about 12 categories of negative life events in the past year, such as the death of a family member, divorce or financial problems.

Extent of social network and loneliness will be assessed with the Social Network Index [59] and the 11 item Loneliness scale [60], respectively.

Assessment of lifestyle characteristics will include smoking, alcohol use, sleep, and physical activities. Smoking behaviour is assessed with standard questions, and the use of alcohol is assessed using the Alcohol Use Disorders Identification Test (AUDIT) [36]. Sleep will be assessed with the Insomnia Rating Scale (IRS) [61]. Finally, the International Physical Activities Questionnaire (IPAQ) [62] will be used to measure energy expenditure based on sports and daily activities. Abilities for self-management of wellbeing will be measured with the Self-Management Abilities Scale (SMAS-30) [63].

Table 1 presents an overview of all instruments applied, including the moment of administration, i.e. at intake (stage one), at baseline (start of stage two), every four months during the first year of treatment, at one-year follow-up or end of treatment when treatment is concluded within one year, and finally at two-year follow-up.

### Statistical analyses

The effect of a determinant on the primary outcome, remission of the index disorder at one year follow-up, will be examined by logistic regression analysis. Depending on the specific objective of specific studies that will be embedded in ROM-GPS, comorbidity between affective disorders can be addressed in different ways. Firstly, comorbidity can be included as a covariate to adjust for the presence of comorbidity. Secondly, by having a sample of well-phenotype patients, a sensitivity analysis on patients with a ‘pure’ affective disorder can be performed. Finally, if theoretically grounded, our research design also allows to examine the interaction between specific comorbid affective disorders and other determinants.

The effect on the secondary outcome, course of symptom severity, will be examined by random coefficient analysis, a specific type of linear mixed models, which takes into account that the repeated assessments of symptom severity are nested within subjects [64]. In random coefficient analysis, the development in the outcome variable is estimated by a straight line and the effect of the determinant on this linear development is tested by the interaction of the determinant with the time of assessment of the outcome variable. All analyses will be controlled for potential confounders.

### Power calculation

Applying logistic regression analysis for the primary outcome variable remission at one-year follow-up, requires a sample size of 231 patients to demonstrate the effect of a continuous determinant with an odd ratio of 1.4 per standard deviation (which is equivalent to a small effect size d of 0.2) with a power of 80% and a significance level of 5%, assuming a one-year remission rate of 50% at the mean of the determinant [65, 66]. With a sample size of 231 patients, ordinary linear regression can demonstrate the effect of a continuous determinant which explains 4% of variance in change in a continuous outcome variable (e.g. change between baseline and follow-up on the secondary outcome measures) with a power of 87%. This power further increases when multiple repeated assessments of the outcome variable (e.g. the four-monthly assessments of symptom severity) are examined as outcome using random coefficient analysis.

To achieve a sample of 231 patients with a complete baseline and follow-up assessment, we estimate that 289 patients have to give informed consent assuming a 20% dropout rate at one-year follow-up [67]. Moreover, assuming an overlap between depressive, anxiety and somatic symptom disorders of at least 50%, analyses per diagnostic main group can be performed when approximately 600 patients have completed the study protocol.

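### At an odds ratio of 1.4, the 231 patients match a one-sided 5% test while the 87% beside it matches a two-sided one; two-sided power at 231 is about 70%, not 80%

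*Protocol article*

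**What the plan says.** All of this is in the protocol article; no separate analysis plan is at hand.

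- **Statistical analyses**, primary model: "The effect of a determinant on the primary outcome, remission of the index disorder at one year follow-up, will be examined by logistic regression analysis". The same section ends: "All analyses will be controlled for potential confounders".
- **Power calculation**, primary outcome: the model "requires a sample size of 231 patients to demonstrate the effect of a continuous determinant with an odd ratio of 1.4 per standard deviation", "with a power of 80% and a significance level of 5"%, taking remission as 50% at the mean of the determinant. The effect is glossed as an "odd ratio of 1.4 per standard deviation (which is equivalent to a small effect size d of 0.2").
- **Power calculation**, secondary outcomes: with the same 231 patients, linear regression is said to have 87% power for a determinant "which explains 4% of variance in change in a continuous outcome variable".
- **Power calculation**, recruitment: "we estimate that 289 patients have to give informed consent", allowing for 20% dropout. The section then gives roughly 600 completers as the point at which analyses by diagnostic main group become possible.

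The significance level is given once, as 5%, without saying whether it is one- or two-sided.

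**The concern.** A 5% level with no further comment is normally read as two-sided. On that reading 231 looks too small for an odds ratio of 1.4 per standard deviation. A one-sided test would need a direction fixed in advance. The article names none for its determinants, which include treatment modality and intensity, drug use, frailty and cognition. In observational data, treatment intensity could be associated with remission in either direction.

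At stake is how a null result is read. If an analysis of about 231 patients finds no association between, say, frailty and remission, a reader will take the chance of having missed the design effect to be 20%. With an ordinary two-sided test it is about 30%.

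**Working it through.** **Inputs (Power calculation section).** Odds ratio 1.4 per SD, so b = ln 1.4 = 0.3365 and b² = 0.1132. Remission P = 0.5 at the mean. Power 80%, z = 0.842. Level 5%: z = 1.645 one-sided, 1.960 two-sided. The determinant is taken as normally distributed.

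**Step 1. Reproduce 231.** Hsieh 1989 formula for one normal covariate:

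n = [z_α + exp(−b²/4)·z_power]² × (1 + 2Pδ) / (P·b²), with δ = [1 + (1 + b²)·exp(5b²/4)] / [1 + exp(−b²/4)].

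Here exp(−b²/4) = 0.972 and δ = 1.157, so (1 + 2Pδ)/(P·b²) = 2.157/0.0566 = 38.11.

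- One-sided: (1.645 + 0.972 × 0.842)² × 38.11 = 6.066 × 38.11 = **231.2**
- Two-sided: (1.960 + 0.972 × 0.842)² × 38.11 = 7.718 × 38.11 = **294.1**

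**Step 2. Try other methods at odds ratio 1.4.**

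| Method | One-sided n | Two-sided n | Two-sided power at 231 | OR with 80% power at 231, two-sided |
|---|---|---|---|---|
| Hsieh 1989 | 231.2 | 294.1 | 69.7% | 1.467 |
| Hsieh 1998, (z_α + z_power)²/[P(1−P)b²] | 218.4 | 277.3 | 72.5% | 1.446 |
| Wald, exact information | 236.8 | 300.7 | 69.0% | 1.475 |
| Wald, null variance for the critical value | 224.6 | 284.2 | 71.7% | 1.454 |

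No two-sided result is near 231. A simulation of 20,000 data sets at n = 231 gave two-sided power of 70.2% (Wald) and 71.1% (likelihood ratio), and one-sided power of 80.6% and 81.0%.

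**Step 3. Reproduce the 87%.** f² = 0.04/0.96 = 0.0417; noncentrality 231 × 0.0417 = 9.625; 1 and 229 degrees of freedom.

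- Two-sided: **87.1%**, which matches.
- One-sided: **92.6%**, which does not.

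**Step 4. Recruitment.** 231/0.8 = 288.75, so 289 follows correctly from 231. With the two-sided requirement: 277.3/0.8 = 346.6 and 300.7/0.8 = 375.8, so about 347 to 376 consents.

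**Step 5. About 600 completers.** Two-sided power for an odds ratio of 1.4 in a pooled, unadjusted model is about 98% (Hsieh 1989).

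**Step 6. Confounder adjustment, for illustration only.** If confounders explain a share R² of the determinant's variance, the effective sample is 231 × (1 − R²). The article gives no R². At assumed values of 0.1, 0.2 and 0.3, two-sided power is about 65%, 60% and 54% (Hsieh 1989), or 68%, 63% and 57% (Hsieh 1998).

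**The case against.** **Rounding of the effect size.** The odds ratio is printed to one decimal and called equivalent to d = 0.2. The simpler two-sided formula returns 231 at an odds ratio of 1.446, which also rounds to 1.4. On that reading both power figures would be two-sided and the fault would be coarse reporting. It cannot be excluded outright, because the sources cited for the method are not at hand. But it replaces the stated input with another. Nor does the d = 0.2 gloss supply it: by the usual conversion, exp(0.2π/√3) = 1.437, which needs 239 to 262 two-sided. At the stated 1.4, only the one-sided calculation fits. A reader might go on to infer that the investigators chose a one-sided test; the article does not say so, and the point does not need it.

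**231 is not the whole study.** This stands. The project is ongoing, clinics were still joining in 2019, no passage makes 231 a stopping point, and about 600 completers are also mentioned. A reader might infer that 231 and 289 are the only targets, or that the cohort as a whole is underpowered. The article does not support either.

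**Adjustment depends on the embedded study.** This largely stands. One article cannot fix a single R² for many determinants, so the loss from adjustment cannot be sized here. What remains is that the figure is for an unadjusted model while every analysis is to be adjusted.

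**Little depends on it.** Effect estimates and the analysis model are unaffected, and on the odds-ratio scale the gap is only 1.4 against 1.45 to 1.48. True, but the power statement is still the yardstick for null results.

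**Conclusion.** The power paragraph is wrong as written. Under a single reading of its 5% level, its two power claims cannot both hold: if two-sided, the 80% is too high; if one-sided, the 87% should be 92.6%. With no one-sided test stated, the two-sided reading is the natural one. Power at 231 for an odds ratio of 1.4 is then about 70% (69.0% to 72.5% across methods). The detectable odds ratio at 80% power is about 1.45 to 1.48, and 80% power for 1.4 needs about 277 to 301 completers.

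This rests on the odds ratio being 1.4 as printed, a normally distributed determinant, 50% remission at its mean, and no covariates. It applies to analyses at about 231 patients, whether pooled or within a diagnostic group, and not to a pooled analysis at about 600. A reader might also infer that adjustment is certain to cut power by a known amount. The documents support only the direction, and only to the extent that confounders correlate with the determinant.

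**What to change.** In the power section:

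1. State that all tests are two-sided at 5%, as the 87% already implies.
2. Restate the primary figure: in an unadjusted model, 231 completers give about 70% power for an odds ratio of 1.4 per SD, or 80% power for about 1.45 to 1.48.
3. If 80% power for 1.4 is kept as the requirement, replace 231 with the figure from one named method (277 to 301) and 289 with the matching number of consents (about 347 to 376). If the odds ratio actually used was not 1.4, print it with enough decimals and name the formula.
4. Add a sentence that these figures are unadjusted and that power falls as confounders correlate with the determinant. Each embedded study can give its own assumed R² and divide the requirement by 1 − R².

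The cost is one reworded paragraph and a less favourable stated power. Enrolment need not change.

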### Ethical issues

The first stage is implemented at the participating outpatient clinics as part of routine clinical care. All patients of the participating mental health organisations are informed in writing at intake that data collected as part of routine clinical care may anonymously be used for research. When the first stage shows that patients meet the in- and exclusion criteria of the study, they are informed orally and in writing about the second stage of the project and are asked whether they may be contacted after one week, to hear whether they want to participate in the study. If so, an appointment is made for the baseline assessment, which starts with and only continues when written informed consent for the study is provided.

Before the start, all relevant documents have been submitted to the ethical review board of the University Medical Center Groningen (METc 2014/106), which concluded that the project is fully in line with the Dutch law (NL47717.042.14). ROM-GPS has been registered at the Dutch Trial Register (NTR6874) (www.trialregister.nl).

### Data-management

Data collection is supported by an online data entry and management system, i.e. Routine Outcome Quality Assessment (ROQUA, see https://www.roqua.nl), developed by the University Medical Center Groningen and the Rob Giel Research center. In case of a self-report questionnaire, patients can choose whether they want to fill in the questionnaire on the computer or prefer a paper and pencil version (which is entered in the online system afterwards by the research nurse).

## Discussion

### Relevance of expected findings

ROM-GPS will produce important new information about the actual effectiveness of interventions for late-life affective disorders in day-to-day mental health care. The population aged 60 or over is growing faster than all younger age groups. Globally, the number of persons aged 60 years will more than double by 2050 to 2.1 billion [68] of which at least every tenth will be confronted with common mental disorders [1–5] and may seek treatment. Knowledge regarding real life outcomes of those treatment is highly relevant in light of the disease burden of this group of disorders. Current treatment strategies, even under optimal circumstances, only achieve modest effects. In depth knowledge of ageing-related determinants as well as their relative contribution on treatment outcome and negative health consequences, may facilitate adaptation of current treatment strategies to address the most important determinants or their consequence more targeted and thus guide the development of new interventions for specific subgroups [69, 70]. Promising examples include psychotherapy adapted to (mild) cognitive deficits [71], optimizing cardiovascular treatment [72], or addressing biomedical frailty [69, 73]. In case of biomedical frailty, for example, antidepressants should be avoided to prevent polypharmacy and falls, while psychological treatment should also address coping with an ageing body (e.g. physiological exhaustion) and should preferably augmented with components of geriatric rehabilitation like protein rich diets and physical exercise. Results may thus directly guide clinical care and may lead to improvement of guidelines by early detection of treatment resistant groups.

ROM-GPS is worldwide the first study in which late-life depressive, anxiety and somatic symptom disorders are studied jointly using a unique hybrid design that combines the possibilities of ROM with more rigorous standardized assessments and follow-up measures. ROM-GPS adds to current practice as the use of (semi-)structured diagnostic psychiatric interviews is not standard practice in the Netherlands. Moreover, only a minority of patients receive ROM [27], despite recommendations in care standards and guidelines [www.ggzstandaarden.nl]. Furthermore, in case ROM is systematically implemented, only a few outcome instruments are used (comparably to our 4 and 8 month follow-up) [74], but no extensive baseline and outcome assessment as implemented in ROM-GPS for those patients giving informed consent. Therefore, our data collection enables to examine the impact of comorbidity on treatment outcome and disease burden. Hopefully, data collection may also assist the development of a better classification for affective disorders in later life. DSM- and ICD-classification systems are often criticized for the (potential) lack of age-neutrality of the criteria for mental disorders [75, 76]. Empirical studies supporting a more optimal age-specific classification, however, are hardly available. Since ROM-GPS includes three groups of extensively phenotyped affective disorders, application of data-driven techniques may be employed to support the development of a classification system that fits more accurately the affective symptoms experienced by older persons.

### Methodological considerations

By collecting these data with the aid of well-trained nurse practitioners or psychologists, the quality of the psychiatric diagnosis of both participants and non-responders is high. Since the first diagnostic assessment is done within the framework of care, research will feel like less of a burden to patients. Moreover, clinicians and patients will benefit as diagnostic data will become directly available for the mental health team. During stage one, data of all patients referred to the participating outpatient clinics are gathered. These data enable us to examine the representativeness of our study sample. In case of selection bias due to differential refusal rates between specific subgroups, findings may be adjusted using ‘propensity score matching’ [77]. To do so reliably, still sufficient numbers of participants are necessary of such subgroups.

The main limitation is probably the burden of the baseline assessment for patients giving informed consent (stage 2). This assessment takes approximately 3–4 h, which may affect patients’ willingness to participate. Nonetheless, our experience with the NESDO study reveals that many patients actually appreciate the thorough investigations done as part of clinical research [23]. Moreover, the assessment can be spread over 2 visits if necessary.

Secondly, we aim to conduct the extensive baseline assessment as soon as possible, but for pragmatic reasons, we consider a period up to 14 days as acceptable. Since symptoms my readily change after the first contact with specialised mental health care, this delay might confound results. Nonetheless, as the time between intake and baseline assessment is known, we can adjust for this time period and where relevant, also can perform sensitivity analyses on the subgroup that was assessed within one week.

### Final conclusion

The ROM-GPS study will show how effective the treatments are which are routinely provided in outpatient geriatric psychiatry, and to what extent this effectiveness is compromised by the typical characteristics of an elderly population. This will indicate whether standard treatments need to be adjusted and supplemented. Furthermore, it will provide a good infrastructure for patient selection for additional studies in our Regional Geriatric Psychiatry Network.

## Data Availability

Researchers interested in using the data, can contact the principle investigator. Data will only be made available in collaboration with the principle investigator and only in case a good research question is formulated, including a hypothesis and an elaborated statistical plan.

## Abbreviations

AGE: Advanced glycation endproducts
ATC code: Anatomical Therapeutic Chemical code
AUDIT: Alcohol Use Disorder Identification Test
DSM: Diagnostic and Statistical Manual of Mental Disorders
GAI: Geriatric Anxiety Inventory
ICD: International classification of diseases
IDS: Inventory of Depressive Symptoms
IPAQ: International Physical Activity Questionnaire
LASA: Longitudinal Aging Study Amsterdam
LSAS: Leibowitz Social Anxiety Scale
MI-A: Mobility Inventory – Avoidance scale
MINI-plus: Mini international neuropsychiatric interview, plus version
MoCA: Montreal Cognitive Assessment
NCEP: National cholesterol education program
NEMESIS: Netherlands mental health survey and incidence study
NEO-FFI: NEO Five Factor Inventory
NESDO: Netherlands study of depression in older persons
PSWQ: Penn State Worry Questionnaire
RCT: Randomised controlled trial
ROM: Routine Outcome Monitoring
ROM-GPS: Routine Outcome Monitoring for Geriatric Psychiatry & Science
SMAS-30: Self-management abilities scale – 30 item version
TFI: Tilburgse frailty index
WHO-DAS: World Health Organisation – Disability Assessment Schedule
WI: Whitley index
